## Abstract

**Introduction:**

India currently has more than 74.2 million people with Type 2 Diabetes Mellitus (T2DM). This is predicted to increase to 124.9 million by 2045. In combination with controlling blood glucose levels among those with T2DM, preventing the onset of diabetes among those at high risk of developing it is essential. Although many diabetes prevention interventions have been implemented in resource-limited settings in recent years, there is limited evidence about their long-term effectiveness, cost-effectiveness, and sustainability. Moreover, evidence on the impact of a diabetes prevention program on cardiovascular risk over time is limited.

**Objectives:**

The overall aim of this study is to evaluate the long-term cardiometabolic effects of the Kerala Diabetes Prevention Program (K-DPP). Specific aims are 1) to measure the long-term effectiveness of K-DPP on diabetes incidence and cardiometabolic risk after nine years from participant recruitment; 2) to assess retinal microvasculature, microalbuminuria, and ECG abnormalities and their association with cardiometabolic risk factors over nine years of the intervention; 3) to evaluate the long-term cost-effectiveness and return on investment of the K-DPP; and 4) to assess the sustainability of community engagement, peer-support, and other related community activities after nine years.

**Methods:**

The nine-year follow-up study aims to reach all 1007 study participants (500 intervention and 507 control) from 60 randomized polling areas recruited to the original trial. Data are being collected in two phases. In phase 1 (Survey), we are admintsering a structured questionnaire, undertake physical measurements, and collect blood and urine samples for biochemical analysis. In phase II, we are inviting participants to undergo retinal imaging, body composition measurements, and ECG. All data collection is being conducted by trained Nurses. The primary outcome is the incidence of T2DM. Secondary outcomes include behavioral, psychosocial, clinical, biochemical, and retinal vasculature measures. Data analysis strategies include a comparison of outcome indicators with baseline, and follow-up measurements conducted at 12 and 24 months. Analysis of the long-term cost-effectiveness of the intervention is planned.

**Discussion:**

Findings from this follow-up study will contribute to improved policy and practice regarding the long-term effects of lifestyle interventions for diabetes prevention in India and other resource-limited settings.

**Trial registration:**

Australia and New Zealand Clinical Trials Registry–(updated from the original trial)ACTRN12611000262909; India: CTRI/2021/10/037191.

## Introduction

Based on recent estimates, there are 537 million people with diabetes globally with 433 million (80.6%) living in low and middle-income countries such as India [1]. The global number of people with diabetes is projected to reach 783 million by 2045. It is estimated that 94% of this increase will occur in low and middle-income countries. Almost 90% of people with undiagnosed diabetes live in low- and middle-income countries [1].

India has the second highest number of people with diabetes (74.2 million), accounting for 1 in 7 of all adults living with diabetes worldwide, and this is expected to increase to 124.9 million by 2045. About 57% of the estimated number of people with diabetes in India are undiagnosed [2]. Partly due to its large population size, India has the second-highest annual number of deaths from diabetes, approximately 0.6 million [1]. In this regard, the prevention and management of diabetes, through community-based approaches need urgent attention [3].

The efficacy, effectiveness, and implementation of lifestyle interventions aimed at preventing the onset of type 2 diabetes have been well-established at least in high-income countries. A review of 38 implementation trials has demonstrated a reduction in type 2 diabetes incidence of between 40–60% [4]. The lifestyle interventions used in these implementation trials have been shown to be more effective when delivered via groups, such as peer support groups. However, most of the trials have been conducted in high-income countries. In addition, there is limited evidence about their effects and sustainability after the active intervention phase.

In this study protocol paper, we briefly discuss the findings of a community-based diabetes prevention program conducted in the Indian state of Kerala, the Kerala Diabetes Prevention Program (K-DPP), from 2013–2016. We also present the rationale to conduct a nine-year follow-up of the original K-DPP participants; the aims, measures to be undertaken, and the analysis plan.

## Summary of Kerala Diabetes Prevention Program (K-DPP) findings at 12 and 24 months

The Kerala Diabetes Prevention Program (K-DPP) is a cluster randomized trial of a group-based and peer-led lifestyle intervention among adults at high-risk for type 2 diabetes in Kerala, India [5]. The intervention was adapted from evidence-based lifestyle interventions implemented in high-income countries, namely, Finland, the United States, and Australia [6]. A total of 60 polling areas (1007 participants) were randomized to the intervention arm (500 participants) or control arm (507 participants) in rural Kerala, India. The intervention was administered over 12 months period. Data on sociodemographic factors, lifestyle or behavioral factors, psychosocial, anthropometric, and biochemical measures were collected at baseline, 12 months, and 24 months. Among K-DPP participants, diabetes had developed in 17.1% of control participants and 14.9% of intervention participants (RR = 0.88; 95% CI: 0.66 -1.16, *P* = 0.36) at 24 months [7]. There was a significant reduction in diabetes incidence among a sub-group of participants with impaired glucose tolerance (IGT) (RR = 0.61, 95% CI: 0.41–0.92) in keeping with findings from the landmark clinical trials conducted on people with IGT [8–10]. The K-DPP program was also associated with a 32% reduction in 10-year cardiovascular disease (CVD) risk in the intervention group compared to the control group (RR = 0.68; 95% CI: 0.47–0.99; *P* = 0.047) among those aged 40 years or more [11]. Effectiveness evaluation has demonstrated significant improvements in certain key CVD risk factors and the physical functioning score of the health-related Quality of life (HRQoL) scale [7]. Moreover, this community-based peer-support lifestyle intervention was found to be cost-effective in individuals at high risk of developing diabetes in India over a 2-year period [11, 12]. The implementation evaluation has shown that the K-DPP program was feasible and acceptable in changing lifestyle behaviors in high-risk individuals [13]. Measures of program reach, adoption, and implementation were excellent for K-DPP. Twenty-nine of the 30 intervention communities delivered all intervention components. Two-thirds of intervention participants attended more than 50% of all peer-led group sessions and program recognition was high among local leaders and champions. There was also very strong community engagement and program sustainability in intervention communities at 24 months with 29/30 groups having conducted other diabetes prevention and health promotion activities in their communities [13].

## Rationale for long-term follow-up of K-DPP participants

### Diabetes incidence and cardiometablic risk

There is limited long-term data on the effect of lifestyle interventions on diabetes incidence and cardiomentabolic risk, especially in low- and middle-income countries. Extended follow-up studies of previous lifestyle intervention studies, such as the Da Qing Diabetes Prevention Study and the U.S. Diabetes Prevention Program, showed benefits in reducing cardiovascular events after many years of follow-up [14, 15]. However, the current evidence is limited and more follow-up studies, particularly from resource-constrained settings, are needed to address this gap. The additional nine years of follow-up in K-DPP enable an assessment of the long-term benefit of lifestyle interventions in terms of reducing diabetes incidence and other cardiometabolic risk. Current and more detailed analyses, including measures of glycemic levels, serum lipids, heart function (ECG), renal function, and the retinal microvaculature, can supplement previous findings. Given the strong study findings and trends at 24 months, it is now important to undertake longterm follow-up to evaluate the program effectiveness, cost-effectiveness, and sustainability of K-DPP.

### Multimorbidity

Diabetes mellitus is one of the main drivers of multimorbidity as it is associated with a large number of risk factors and complications [16]. Consequently, patients with type 2 diabetes mellitus often live with and develop multiple co-occurring conditions with negative impacts on disease management and quality of life [17]. Given the rich baseline and short-term follow-up data from people at high risk of diabetes at enrolment, K-DPP would enable an analysis of progressive development of various multimorbidities, including heart disease and kidney disease, over time in the study population. It also enables evaluation of the association between multimorbidity and glycemic levels in this population.

### Retinal vasculature

Changes in the retinal microvasculature, such as retinal arteriolar narrowing, venular dilatation, and retinopathy, have been associated with various systemic conditions, including impaired fasting glucose, obesity, blood pressure, incident hypertension, incident diabetes, and cardiovascular disease [18]. Retinal vascular calibre has been shown, in prospective cohorts, to be a predictor of type 2 diabetes and impaired fasting glucose. More recent studies and analyses implicate that a wider retinal venular calibre is a marker of chronic hyperglycemia, prediabetes, and microvascular complications of diabetic retinopathy and nephropathy [19]. Wider retinal venular calibre has also been associated changes in body composition, carotid artery disease, incident coronary heart disease, and incident stroke [20]. As compared to retinal venular changes, retinal arteriolar changes are more predictive of hypertension-related comorbidities [21]. Retinal vascular geometry alterations are a novel marker to predict the progression of retinopathy [22]. A follow-up study of K-DPP enables evaluation of the differences in the retinal vasculature between the intervention group and control group who were at high risk for diabetes at enrolment. It will also enable an analysis of anthropological and metabolic parameters that influence retinal vasculature measurements and their differences between groups.

## Methods

### Study aims

The overall aim of this study is to evaluate the long-term effects of the K-DPP on diabetes incidence and cardiometabolic risk at nine years following participant recruitment.

The specific objectives are:To estimate the effects of K-DPP on diabetes incidence and cardiometabolic risk at nine yearsTo assess retinal microvasculature, microalbuminuria, and electrocardiogram (ECG) abnormalities and their association with incident diabetes and cardiometabolic risk factorsTo evaluate the cost-effectiveness and return on investment of the K-DPP at nine yearsTo assess the sustainability of community engagement, peer support, and other related community activities after nine years

### Study design and setting/context

The current study is the nineth-year follow-up assessment of the K-DPP. The protocol paper for the original trial has been published elsewhere [5]. K-DPP was a cluster RCT conducted in 60 polling areas (clusters, electoral divisions with geographical boundaries) of *Neyyattinkara* taluk (subdistrict) in Trivandrum district, Kerala state, India. Participants were screened and recruited in 2013 and the 12-month intervention was completed in 2013–2014 [23, 24]. The study area has been affected by floods during monsoon season in more recent years [25]. particularly the study areas of Kattakada and Neyyatinkara. The continuum of care for chronic diseases during this period was affected adversely due to the impact on access to care and increased risk of other medical conditions. The recent COVID-19 pandemic has also severely affected the study area with cases peaking in October 2020, May 2021, and August 2021 [9]. Additionally, travel restrictions during lockdowns during COVID pandemic posed discontinuities in NCD care [26].

### Study population

The study population for K-DPP is adults 30–60 years of age who were at high risk for diabetes based on the Indian Diabetes Risk Score (IDRS ≥ 60) [27] at the time of enrolment. Of the total 1007 participants who were enrolled in K-DPP, 47% were females. Each peer group selected two peer leaders (one male and one female) from among the participants with the assistance of the intervention team. The 60 peer groups each with 10 to 23 participants had an approximately equal number of males and females. The peer leaders were trained by the intervention team consisted of an intervention manager and an intervention assistant to deliver the intervention [7].

### Sample size

#### Primary outcomes

Based on the available data at 12 and 24 months, we anticipate more than 90% of K-DPP participants at baseline can provide complete and valid data for all key measures underlying diabetes incidence and 10-year CVD risk predicted using the Framingham Risk Score [28] at nine years. The proportion of participants (≥ 40 years of age at baseline) at high-rosk of CVD (with a predicted 10-year CVD risk greater than 20% [29]) is expected to be 34.5% in the control arm (*n* = 348) versus 17.9% in the K-DPP arm (*n* = 337) after nine years, assuming a linear increasing trend overtime based on our data so far. The power to detect this difference is more than 97% when accounting for an intra-cluster correlation of 0.02 at a two-sided 5% level of significance.

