Assessment of heart conditions		ECG	X	X	X	✓
Retinal microvasculature		Retinal imaging measures(Retinal architecture, arteriolar and venular diameters, and tortuosity) [44]	X	X	X	✓
Mortality		Status and self-reported causes of death	X	X	X	✓
Economic Evaluation	Healthcare utilization	Direct and indirect costs associated with outpatient and inpatient healthcare services, sources of financing, and time away from work due to ill health + SF-36	✓	✓	✓	✓
Community engagement	Sustainability	Sustainability – continued engagement in peer groups/activities; contacts with peer leaders; intention to continue engagement	X	X	X	✓

*WHO* World Health Organization, *SF-36*  Short Form 36, *MESA* Multi-Ethnic Study of Atherosclerosis, *OGTT*  Oral Glucose Tolerance Test, *TBC*  Total Blood Cholesterol, *HDL* High Density Lipoprotein, *LDL* Low Density Lipopotein

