### Statistical analysis

The two co-primary outcomes are diabetes incidence and CVD risk. The analyses will observe the intention-to-treat principle. A generalized estimating equation [46] model with appropriate link function and robust standard errors to account for clustering at polling areas will be fitted to estimate the relative risk (and 95% CI) for the co-primary outcomes at nine years. The sensitivity of the results to assumptions on the missing outcome data underlying this model will be examined using the method of multiple imputations to handle missing data and a pattern-mixture model.

To evaluate the treatment effect on continuous outcomes, a repeated measures mixed-effects linear regression model, adjusting for the baseline measures, will be fitted. Any skewed continuous outcome variable may be transformed before fitting this model. The model will specify treatment, time-point, and treatment by time-point interaction as fixed effects. Random effects will be specified for polling areas, to account for the clustered study design, and for participants, to account for correlation between the repeated measurements on the same participant. The estimated treatment effect (e.g., the absolute difference in means between the treatment arms) at nine years and two-sided 95% CI will be obtained. Binary other outcomes (e.g., diabetes) will be analyzed using GEE models similar to that of the co-primary outcomes.

The retinal image measurements will be compared between the treatment and control groups on the impact of a lifestyle modification program on pre-clinical changes in the retinal microvasculature and its correlation with cardiometabolic risk factors. Retinal imaging measures will include measures retinal architecture such as arteriolar and venular diameters and tortuosity.

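### The CVD co-primary is a predicted risk score at year nine, with no stated rule for participants who have died or already had a CVD event by then

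*Protocol article*

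**What the plan says.** The Statistical analysis section states: "The two co-primary outcomes are diabetes incidence and CVD risk". It estimates a relative risk for each at nine years, using GEE with robust standard errors under intention to treat. CVD risk is therefore treated as binary. Multiple imputation and a pattern-mixture model appear there as sensitivity analyses for missing outcomes.

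The only definition of the binary outcome is in Sample size, Primary outcomes. The instrument and time point are "10-year CVD risk predicted using the Framingham Risk Score [28] at nine years". High risk means "with a predicted 10-year CVD risk greater than 20" per cent, and the group is introduced as "The proportion of participants (≥ 40 years of age at baseline". The proportion at high risk "is expected to be 34.5% in the control arm (*n* = 348) versus 17.9% in the K-DPP arm (*n* = 337) after nine years". The article adds: "The power to detect this difference is more than 97" per cent, with an intra-cluster correlation of 0.02 and a two-sided 5% level.

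Table 1 lists, at nine years only, a mortality item ("Status and self-reported causes of death") and a multimorbidity questionnaire. Medical history, including CVD medications, is collected at every round. None of these items is linked to the CVD co-primary.

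**The concern.** The score looks forward ten years from year nine. It cannot be calculated for someone who has died, and it does not register an event that has already happened. A survivor whose measured risk factors are controlled, for example on treatment, can fall at or below the cut-off and be counted with the favourable outcomes.

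This mattered less at 24 months. Nine years after recruiting high-risk adults aged 30 to 60, deaths and CVD events are foreseeable, and the new mortality item shows that the sponsor expects some deaths. The expected completeness above 90% is drawn from the 12- and 24-month rounds. The Secondary outcomes paragraph illustrates missing data only by loss to follow-up or no blood sample. Nothing separates death from other missing outcomes.

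At stake is the meaning of a co-primary result. If deaths and events differ by arm, the score comparison is between selected survivors and no longer between the groups as randomised.

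**Working it through.** **1. The plan's own figure.** Inputs from Sample size, Primary outcomes: 34.5% of 348 against 17.9% of 337, intra-cluster correlation 0.02, two-sided 5%. There are 60 clusters, taken as 30 per arm. Design effect = 1 + (m − 1) × 0.02.

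- m = n/30 (11.6 and 11.2): design effects 1.212 and 1.205, power 99.5%.
- m = 1007/60 = 16.8: design effect 1.316, power 99.2%.
- m = 16.8 with 90% retained: 98.5%.
- m = 16.8 with 18% (control) and 22% (intervention) missing: 97.3%.

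The stated "more than 97%" is reproduced. The point concerns the outcome definition, not the power.

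**2. How many people could be affected.** The documents give no rate of CVD events or deaths. Assume 4% to 8% by year nine among 348 + 337 = 685:

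- 0.04 × 685 = 27; 0.08 × 685 = 55.
- Expected high-risk cases: 0.345 × 348 + 0.179 × 337 = 120 + 60 = 180.

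**3. Effect on the relative risk.** Let e_c and e_i be the assumed proportions with a CVD event or CVD death in control and intervention. Take 34.5% and 17.9% as the high-risk proportions among event-free survivors.

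- Score only, event-free: 0.179/0.345 = 0.52.
- Events counted as adverse: (0.179 + 0.821 e_i)/(0.345 + 0.655 e_c).
- Events all counted as not high risk (an extreme, since some survivors will score above 20% and the deceased are not scored): 0.179(1 − e_i)/[0.345(1 − e_c)].

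| Assumed e_c / e_i | Score only | Events as not high risk | Events as adverse |
|---|---|---|---|
| 7% / 5% | 0.52 | 0.170/0.321 = 0.53 | 0.220/0.391 = 0.56 |
| 10% / 7% | 0.52 | 0.166/0.311 = 0.54 | 0.236/0.411 = 0.58 |
| 10% / 3% | 0.52 | 0.174/0.311 = 0.56 | 0.204/0.411 = 0.50 |

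**4. Direction.** Counting events gives a relative risk below the score-only 0.52 only if 0.821 e_i < 0.5188 × 0.655 e_c, that is e_i/e_c < 0.3398/0.821 = 0.41. Above that ratio the score alone looks more favourable than the outcome with events counted; below it, less favourable. The first two rows and the third row show the two cases.

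**5. No true difference.** Suppose the total with an event or a high score is 34.5% in both arms, and assume 5% control and 10% intervention events.

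- Event-free: (0.345 − 0.05)/0.95 = 31.1% against (0.345 − 0.10)/0.90 = 27.2%, relative risk 0.88.
- Events as not high risk: 0.245/0.295 = 0.83.

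The score then suggests a benefit where the total burden is equal. The event-free comparison would reach significance about 16% of the time.

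**The case against.** The strongest reply is that this is an omission in a condensed article. The cut-off stands in a sample-size paragraph, and rules for deaths and prior CVD are commonly left to an analysis plan or to the cited original protocol, neither of which is shown. That has weight: the article does not say that event survivors will be counted as not high risk. What stands against it is that the outcome which is fixed cannot exist for the deceased and ignores past events, so applying it literally gives a survivor comparison. Any later rule would have to alter the stated outcome.

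Three stronger readings are tempting and are not supported.

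- A reader might infer that, if the programme prevents events, the score-only relative risk is pulled toward 1. With 7% against 5% events it is the reverse: 0.52 on the score and 0.56 with events counted.
- A reader might infer that the plan will impute scores for the deceased. Imputation appears only as a sensitivity analysis; in the main GEE these participants drop out. The article merely fails to set them apart.
- A reader might infer that CVD events go unrecorded. Cause of death is collected and multimorbidity is a secondary outcome; these items just do not enter this endpoint.

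It is also fair that the no-difference example needs more events in the intervention arm, which nothing in the documents suggests. Nor is it clear whether 348 and 337 are all participants aged 40 or more or only those expected to give data.

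**Conclusion.** The point holds as a gap in the definition of a co-primary outcome. As stated, deaths leave the main analysis, and a CVD survivor can be classed as not high risk. The bias can go either way. Its size is unknown because no event rate is given. With assumed rates of 7% and 5% the relative risk shifts by 0.04, from 0.52 to 0.56; larger or more unequal rates shift it more. These figures assume that the planned 34.5% and 17.9% apply to event-free survivors. The conclusion does not depend on any error in the power calculation, and it does not show that the co-primary must be replaced by a composite. A classification rule with a pre-specified companion analysis is enough.

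**What to change.** Follow-up is still running, so the following can be stated before data are analysed:

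1. A participant with a non-fatal CVD event since baseline, or a CVD death by year nine, is classed as having the adverse outcome. Use the vital status, cause of death, medical history and multimorbidity items.
2. No risk score is imputed for anyone who has died. Non-CVD death is handled separately, for example as a competing event, and not as ordinary missing data.
3. The score-only result in event-free survivors is reported alongside, for continuity with 24 months.
4. If the sponsor prefers to keep the score-only co-primary, the version with events counted is pre-specified as a key sensitivity analysis.

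The main cost is wording, as the rule uses items already listed in Table 1. The sponsor should confirm that the questionnaires record CVD events and their timing, since the table describes medical history by medications. Event history and cause of death are self- or family-reported, and direct comparability with the 24-month outcome is slightly reduced. Power stays high if event rates are equal in the arms: 98.5% at an assumed 5% and 96.6% at 10% (m = n/30, no other missing data). It would fall to about 88% if the assumed rates were 10% in control and 13% in intervention.
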